#### Evaluating the effectiveness of SFL- data analysis

Questionnaire data is analysed using Statistical Packages for the Social Sciences (SPSS V 24). Descriptive statistics for each variable are calculated to inform participant characteristics. Intervention effect on health and wellbeing outcomes are determined by comparing the change scores from baseline to 3, 6 and 12 months, comparing data using inferential tests to identify significant differences set at *p* = 0.05. Analysis of subgroups based on criteria such as; Shed size location and timing of the intervention, will also be performed to identify significant differences in intervention effect between groups. Outcome data obtained from all participants are included in the data analysis, regardless of adherence to SFL. The intervention effects will be assessed at 3, 6 and 12 months based on those who completed follow-up at these time points. Assuming a worst case scenario for absentees i.e. that absentees failed to achieve a significant improvement in core health outcomes (physical activity, diet, mental wellbeing, subjective wellbeing, social capital and help-seeking), these worst- case scenario analyses will reflect the intention to treat principle. The numbers who achieved significant improvement at 3, 6 and 12 months will be presented as a percentage of those who were tested at these follow-up points. For the initial intervention effect worst-case scenario, the numbers who achieved significant improvements at 3 months will be presented as a percentage of those who were tested at baseline. The worst-case scenario for maintenance of this initial intervention effect will present the numbers who achieved significant improvements at 6 and 12 months as a percentage of those who were tested at the 3 month follow-up. Observed success rates will be compared between the intervention and comparison group in waiting using Chi-Square analysis.

A hybrid analytic approach of inductive and deductive analysis is applied to the participant transcripts. This means that whilst implementation frameworks are applied to inform implementation outcomes, the analysis process will remain open to findings that may emerge outside of those pre-set domains to allow assessment of intervention effect. In these circumstances, inter-rater reliability is used to cross-check coding strategies and interpretations are negotiated to agree on a ‘master’ code list.

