Sheds are a community-based, grassroots movement which originated in Australia and have since grown exponentially in Ireland. Sheds have long been recognised not just as a suitable setting in which to actively promote and engage men in health but also as being imbued with inherent and organic health promoting qualities [26]. Sheds are autonomous grass roots spaces which are non-structured and informal, varying in size and resources. Sheds offer a safe and familiar environment for Shed members (‘Shedders’) and foster a sense of social support, belonging and camaraderie, through developing new skills, shared projects, activities, goals and decision making [27]. All of these factors have been linked with enhancing the health and wellbeing of the men who attend with social support, in particular, being frequently reported as a key enabler of men’s help-seeking [28]. The enhanced sense of belongingness that is attributed to the non-conventional setting of Sheds increases their appeal to typically HTR men [29–31]. This is also the case in more recent research which suggests that the Sheds have a protective effect against loneliness [32]. The inherent health promoting qualities of Sheds therefore present a strong foundation upon which to build structured health promotion programmes. Moreover, drawing from a rich source of past interventions that utilised strengths-based and gender-specific approaches, the Men’s Sheds setting is well-positioned to deliver tailored, targeted health promotion initiatives to what has been traditionally regarded as an inaccessible of HTR cohort of men [33]. Nevertheless, it is also critically important that such endeavours enrich rather than erode the ethos of the Shed environment, which means that programmes need to be pragmatically evaluated with Shedders at the centre of decision making [33, 34]. Conventional wisdom dictates that health interventions need to be delivered systematically, to be context free, with strict inclusion criteria. However, Sheds are not just highly variable, autonomous, non-structured spaces; these are the very characteristics that define the essence of Sheds and which need to be respected in order to uphold the integrity and ethos of the Sheds. The challenge therefore is to develop a pragmatic delivery design that can operate within an organic, non-structured space, where contextual factors vary, where attendance can be sporadic, and where there is no compulsion on members to undertake any activity.

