#### Participants and sampling

Respecting the autonomous and informal environment of the Sheds is an important factor in delivering health promotion through Sheds [27, 33]. Therefore, Sheds are recruited to participate in the SFL programme and evaluation via purposive sampling using an expression of interest process with the objective to deliver SFL in a diverse range of Shed settings (small/large, urban/rural). All adult males in the Sheds setting were eligible to participate in the study providing they had good proficiency of the English language and could give informed consent. A sample size estimation was undertaken using G*Power 3.1.9.2 software using physical activity (PA) as the key outcome measure, whereby it was calculated that 106 participants would be required for a trial in which participants were individually randomised (the decision to use PA as the primary outcome measure was determined through consultation with Shedders who requested that PA be a key focus of SFL during the initial pilot phase). However a clustered design in which SFL was delivered to small clusters of men within Sheds was more preferable to honour the Shed ethos whilst also ensuring a wide geographical spread. For this reason a design with circa 20 men in each cluster was estimated. A previous study with middle-aged men suggested that this design effect is ~ 2.4, thus increasing the sample size required to 255 [47]. Allowing for a 20% dropout based on a sample size estimation, the final total required was 306 or 15 clusters. In the event of low participation within clusters, it was decided that SFL would be targeted at clusters with similar representation. In Phase 1, 421 Shedders participated across 22 clusters and these were divided into two cohorts. Whilst delivery occurred in the first cohort (*n* = 12 clusters; *n* = 212 Shedders) a wait list control cohort served as a comparator (*n* = 3 clusters; *n* = 89 Shedders) and these were a subset of the second cohort (*n* = 9 clusters, *n* = 209 Shedders). Fourteen clusters were in urban areas and 8 were in rural areas across counties; Kildare (in Ireland’s mid-east region with a population of ca. 222, 504), Waterford (in Ireland’s south-east region with a population of ca. 116,176), Limerick (in Ireland’s south-east region with a population of ca. 194,899) and Louth (in Ireland’s mid-east region with a population of 128, 884) [48]. Participants were recruited for Phase 1 across Waterford and Kildare in March to May 2019 and Limerick and Louth in September to December 2019. Participants for Phase 2 will be recruited from September to December 2021 (recruitment was postponed until this date due to COVID-19 restrictions).

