#### Evaluating the effectiveness of SFL- data collection

Questionnaires are administered to participants by a research team member trained in data collection procedures to ensure standardised measurement and questionnaire administration. Questionnaires are administered one-to-one in the Sheds setting to account for potential literacy issues, prevent respondent burn-out, limit missing data and build rapport and trust between the researchers and Shedders. To also minimise missing data, participants will be contacted by the IMSA in the days before the research team visit the Sheds to perform data collection. Due to the informal nature of the Sheds, absence of data for a participant does will not necessarily indicate dropout from SFL. During 6 and 12 month follow-up in Phase 1, Cohort 2 were experiencing COVID-19 restrictions and therefore questionnaires were administered via phone in order to promote participant retention and complete follow-up. The questionnaire was designed via a consultation process with stakeholders involved in the design and delivery of SFL with a view to optimising acceptability for SFL participants and also SFL providers who were interested in evaluating their individual components of SFL. Participant demographics are recorded at baseline and include date of birth, living arrangements, educational attainment, employment status relationship and ethnicity. Participants are also asked how long they had been a Shed member and how often they attend the Shed. Core health and wellbeing outcomes measured at all-time points up to 12 months consist of; subjective wellbeing, help-seeking, physical activity, mental wellbeing, diet and cooking skills, social capital and self-efficacy. Participants are also asked how often they seek information about their health.

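### Change in loneliness, social capital and mental wellbeing may partly reflect Shed membership rather than SFL; recorded membership length is not used to check this, and no comparator is described at 6 and 12 months

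*Protocol article*

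**What the plan says.** **Analysis.** In the data-analysis section of Part 1 (effectiveness), "Intervention effect on health and wellbeing outcomes are determined by comparing the change scores from baseline to 3, 6 and 12 months", with "significant differences set at *p* = 0.05". All participants with outcome data are included. The same section adds a between-group test: "Observed success rates will be compared between the intervention and comparison group in waiting using Chi-Square analysis". The subgroup criteria given as examples are Shed size, location and timing.

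**Comparator.** Under Participants and sampling, during delivery in cohort 1 (12 clusters, 212 men) "a wait list control cohort served as a comparator". This group is 3 clusters and 89 men, a subset of cohort 2. On timing: "Participants were recruited for Phase 1 across Waterford and Kildare in March to May 2019 and Limerick and Louth in September to December 2019". The Limitations section states that the design is not randomised.

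**Eligibility.** "All adult males in the Sheds setting were eligible to participate in the study", given adequate English and informed consent. No minimum length of membership is set.

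**Shed effect.** The Background section on Men's Sheds links features of Sheds with members' health and wellbeing, and cites recent research suggesting that "the Sheds have a protective effect against loneliness".

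**Data held.** The data-collection section says that "Participants are also asked how long they had been a Shed member and how often they attend the Shed". Loneliness before joining the Shed is also rated retrospectively at baseline.

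**The concern.** The question for SFL is what it adds to what a Shed already offers. Loneliness, belonging, trust, close support and mental wellbeing are SFL outcomes, and they are the kind of outcome that the article associates with Sheds themselves. A man who joined shortly before baseline might improve over the following months with or without SFL. A change score with no comparator would credit that improvement to SFL.

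Length of membership is the recorded variable that bears most directly on this explanation, yet no effect analysis in the article names it. The one between-group test that is named takes no baseline variable into account, although the groups are self-selected Sheds in different counties and the comparator has only three of them.

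At stake is how the wellbeing and social results are read, including in the impact report planned after Phase 1. Physical activity, the outcome used for the sample size, is not the main worry here.

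**Working it through.** The plan gives no figure on this point to reproduce. The check sets the passages side by side and then gives an illustration with stated assumptions.

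**1. Which analyses are exposed**
- *SFL v wait-list, while cohort 1 receives SFL.* Both groups are Shedders. With shares of recent joiners f_I and f_C and a Shed-only gain D, bias = (f_I - f_C) x D. It is zero if the shares are equal.
- *Change at 6 and 12 months.* The comparator is described only during delivery in cohort 1, and cohort 2 went on to receive SFL. With no concurrent comparator, bias = f x D, where f is the overall share.
- The sentence on change scores does not say whether the comparison is within or between groups. The second formula applies to the within-group reading, which is the only one available where no comparator exists.

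**2. Inputs**
- From the article: 421 men in Phase 1; 212 in cohort 1 and 89 in the wait-list group; design effect about 2.4; 20% dropout allowance; significance at 0.05.
- Assumed, because the article gives neither: f = 10-40%; D = 0.2-0.5 SD of change.
- Also assumed: a two-sided test, and that 2.4 applies to change scores.

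**3. Inflation of an uncontrolled change, f x D**
- Lowest: 0.10 x 0.2 = 0.02 SD.
- Middle: 0.20 x 0.5 = 0.10 SD.
- High: 0.30 x 0.5 = 0.15 SD.
- Highest: 0.40 x 0.5 = 0.20 SD.

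On the SWEMWBS scale, an assumed D of 2 points (the change that the article calls relevant) with f = 10-30% gives 0.2-0.6 points.

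**4. Smallest significant mean change, 1.96 x sqrt(2.4/n)**
- All 421 men: SE = sqrt(2.4/421) = 0.0755; cut-off 1.96 x 0.0755 = 0.148 SD.
- After 20% dropout, n = 0.8 x 421 = 337: SE = sqrt(2.4/337) = 0.0844; cut-off 0.165 SD.

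With D = 0.5 the share needed to reach the cut-off is 0.148/0.5 = 30%, or 0.165/0.5 = 33% after dropout. With D = 0.2 it is 74% or 83%, well outside the assumed range.

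**5. Chance of a significant benefit if SFL adds nothing, Phi(bias/SE - 1.96)**

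| Bias (SD) | 421 men | 337 men |
|---|---|---|
| 0.10 | 26% | 22% |
| 0.15 | 51% | 43% |
| 0.20 | 75% | 66% |

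The nominal figure in that direction is 2.5%.

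**6. The wait-list contrast**
If the control share were half the SFL share, the bias would be half the figures in step 3, or 0.01-0.10 SD. For scale, the cut-off for a difference in mean change is 1.96 x sqrt(2.4 x (1/212 + 1/89)) = 1.96 x 0.196 = 0.38 SD. The test named is on success rates, so this is only a guide. It suggests that an imbalance would shift the estimate and would be unlikely to create a significant result unaided.

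**The case against.** The strongest reply is that the design is controlled. Table 2 calls it a pragmatic controlled trial, the wait-list men are Shedders, and a general Shed effect acts in both groups. That stands: where the comparator exists, only an imbalance in membership length matters. It does not reach 6 and 12 months, and with three non-randomised comparator clusters balance cannot be taken for granted.

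Second, a reader might infer that the article says joining a Shed improves wellbeing. It does not. It reports a link and research that suggests protection against loneliness. A reader might also infer that recent joiners took part in numbers, drawn in by the free health check and other hooks. The article never says so. Recent joiners are simply not excluded, and the hooks are described as engaging men in the programme, not in Shed membership.

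Third, choice of covariates usually belongs in an analysis plan, and the subgroup list is open-ended. That is fair for the subgroup list, and silence alone would be a weak ground. But the unadjusted chi-square is a stated choice, and so is defining the effect through change scores at times with no described comparator.

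Fourth, the direction at later times is uncertain. Cohort 2's 6- and 12-month follow-up fell under COVID-19 restrictions, so a steady Shed-driven gain cannot be presumed. This stands.

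Fifth, stratifying by membership length does not isolate the Shed effect. Established members still give an uncontrolled before-after change, and a larger change in newcomers could mean that SFL works better in them. This also stands. It is why the stratified result should be a sensitivity analysis and why no claim should depend on one subgroup.

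**Conclusion.** The concern holds in a limited form. For loneliness, social capital and mental wellbeing, the 6- and 12-month change scores cannot distinguish gains from SFL from gains that Shed membership might bring, and the named wait-list test does nothing about a possible imbalance in membership length.

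The size is unknown because both the share of recent joiners and their Shed-only gain are assumptions. Over 10-40% and 0.2-0.5 SD the inflation is 0.02-0.20 SD. The low end is negligible. Only the top, roughly 30% or more recent joiners each gaining 0.5 SD, reaches the cut-off of about 0.15 SD, or 0.17 SD after dropout. It is tempting to conclude that a bias of 0.15 SD would by itself produce a significant SFL effect. It would do so about half the time with full follow-up and less often after dropout.

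The documents do not support saying that the SFL effect is an artefact of joining, or that the wait-list contrast is biased. They support saying that the plan leaves an available check unused and does not mark its later results as uncontrolled.

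**What to change.** In the data-analysis section of Part 1:

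1. Replace the unadjusted chi-square comparison of SFL and wait-list with a regression that adjusts for baseline length of Shed membership and allows for clustering by Shed.
2. Report the 3-, 6- and 12-month changes by length of membership as a sensitivity analysis, with any categories fixed in advance, and give the distribution of membership length in each group.
3. State that the 6- and 12-month changes have no concurrent comparator, and that a difference by membership length may also reflect a different SFL effect in newcomers.

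The variable is already collected, so the cost is wording, a little more analysis and slightly wider intervals. Adjustment does not supply the missing later comparator, and three wait-list clusters will keep the between-group estimate imprecise.

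### Physical activity is named primary and used to size the trial, but the analysis section gives it no deciding test or visit and applies p = 0.05 to health and wellbeing outcomes at 3, 6 and 12 months

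*Protocol article*

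**What the plan says.** All of the relevant text is in Part 1 of the protocol article.

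- **Participants and sampling.** The sample size was estimated "using physical activity (PA) as the key outcome measure". The same sentence records that "the decision to use PA as the primary outcome measure was determined through consultation with Shedders". The required numbers (106, then 255, then 306) all follow from that choice.
- **Data collection.** "Core health and wellbeing outcomes measured at all-time points up to 12 months consist of" seven domains: "subjective wellbeing, help-seeking, physical activity, mental wellbeing, diet and cooking skills, social capital and self-efficacy". Table 2 lists the same seven.
- **Data analysis.** The effect on health and wellbeing outcomes is judged from change scores to 3, 6 and 12 months, "comparing data using inferential tests to identify significant differences set at" p = 0.05. A later sentence states: "The intervention effects will be assessed at 3, 6 and 12 months based on those who completed follow-up at these time points". PA is mentioned once, in the sentence on the worst-case handling of absentees, inside a bracketed list of "core health outcomes (physical activity, diet, mental wellbeing, subjective wellbeing, social capital and help-seeking". That list has six members and omits self-efficacy.
- The same section adds subgroup comparisons and a chi-square comparison of success rates with the waiting group. It names no primary test and no primary visit. It describes 3 months as the initial effect and 6 and 12 months as its maintenance, but only when defining the worst-case denominators.

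**The concern.** A primary outcome serves two purposes: it sets the sample size, and it identifies the result on which the claim of effectiveness will stand or fall. Here PA does the first and not the second. The analysis section sets one threshold for a family of outcomes at three visits and treats PA as a member of that family.

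Two things follow. The 5% level no longer describes the chance of a false claim that the programme works, because several results could each support that claim. And a null PA result could be passed over in favour of whichever other outcome or visit reached p = 0.05. The Table 2 effectiveness question, which covers knowledge, attitudes, outcomes and behaviours together, could then be answered yes on that basis.

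The published text carries extra weight in this study. Registration was retrospective (March 2021), Phase 1 recruited in 2019, and the Discussion says the findings will inform decisions on effectiveness and scale-up.

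**Working it through.** **1. The plan's own figures.** The sizing based on PA reproduces as 106 × 2.4 = 254.4, rounded up to 255, and 255 × 1.2 = 306. (Dividing by 0.8 would give 319, which is a separate matter.) The only error rate stated in the article is p = 0.05. Sidedness and a family-wise rate are not given, so there is no overall error figure to reproduce.

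**2. Number of tests (assumed).** One test per core domain per visit gives 6 × 3 = 18 using the analysis section's list, or 7 × 3 = 21 using the data collection list. Subgroup and chi-square comparisons are left out because their number is not fixed.

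**3. Independent tests, no true effect anywhere.**
- Any false significant result: 1 − 0.95^18 = 0.603; 1 − 0.95^21 = 0.659.
- A false benefit, with two-sided tests (0.025 in the favourable tail): 1 − 0.975^18 = 0.366; 1 − 0.975^21 = 0.412.

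**4. Correlated tests.** The article gives no correlations, so these are assumed. Test statistics were simulated as multivariate normal with the stated correlations between outcomes and between visits; the correlation between different outcomes at different visits is the product of the two.

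| Between outcomes / visits | 18 tests, either direction | 18 tests, benefit | 21 tests, either direction | 21 tests, benefit |
|---|---|---|---|---|
| 0.3 / 0.5 | 0.515 | 0.274 | 0.562 | 0.302 |
| 0.3 / 0.7 | 0.462 | 0.241 | 0.509 | 0.266 |
| 0.5 / 0.7 | 0.403 | 0.204 | 0.442 | 0.224 |

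**5. PA alone at three visits.** If only PA counted but any of its three visits could decide, the either-direction error would be 1 − 0.95^3 = 0.143 under independence. By the same simulation it is 0.126 with correlation 0.5 between visits and 0.109 with 0.7. Naming PA without naming a visit therefore still leaves the error at 11 to 14%.

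**6. After the fix.** One test of PA at one visit has error 0.05 by construction.

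**The case against.** **A condensed article may leave this to the analysis plan.** A multiplicity rule, a test hierarchy and a choice of scale per domain are commonly settled there, and their absence is no fault here. That is accepted. What remains is a mismatch within the article: one section names a primary outcome, and the section that says how effectiveness is judged sets a threshold for health and wellbeing outcomes generally and gives PA no distinct role. Following the analysis section as written gives the inflated error.

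**The text is less explicit than a quick reading suggests.** The six-outcome list is in the absentee sentence, not the one with the threshold. The article does not say that the outcomes rank equally or that adjustment is ruled out, and it states no level for the subgroup tests. These points stand, so 18 to 21 is an assumed count. The visits are also partly distinguished, as initial effect and maintenance, though no visit is named as primary. The wait-list group is described as the comparator while the first cohort received the programme, so it is unclear whether controlled comparisons at 6 and 12 months are intended.

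**A stronger reading is tempting.** A reader might infer that a false significant benefit is more likely than not. The documents do not support that. The 60 to 66% figure needs independent tests and counts false harms as well as false benefits. With two-sided tests, a false benefit over 18 to 21 tests stays below one half even under independence. It passes one half only under choices the article does not make. One is one-sided testing at 0.05 with low correlation (60 to 66% if independent). Another is testing separately each of the 21 or so core scores that can be counted in Table 2, at three visits: 63 tests, 0.80 if independent and 0.38 to 0.67 for between-outcome correlations of 0.1 to 0.5.

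**A visit chosen now is late for Phase 1.** Cohort 2's 6- and 12-month follow-up is already described in the past tense, and some interim findings have been published. This also stands. It is a reason for disclosure, not for leaving the primary test undefined.

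**Conclusion.** The point holds. PA is primary in the sizing text and is not carried into the analysis text, where no single result is identified as deciding effectiveness.

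On an assumed count of one test per core domain per visit, the chance of at least one false significant result is 60 to 66% if independent and about 40 to 56% under the assumed correlations. For a false benefit from two-sided tests it is 37 to 41% and about 20 to 30%. A single two-sided 5% test allows 5% and 2.5% respectively. All figures assume no true effect on any outcome and exclude subgroup and chi-square tests. The correlations and the test count are assumptions, but within these ranges the error stays far above the nominal level.

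The six- and seven-item core lists are a smaller inconsistency that also changes the count.

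**What to change.** In the effectiveness data analysis section:

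- State that PA, compared between SFL and wait-list at one named visit, is the single confirmatory test at two-sided 5%. Three months fits best with the article's own description of the initial effect and with the period in which the wait-list group is a comparator. Say which PA score is meant, since Table 2 lists a walking measure beside it.
- Label all other outcomes, visits and subgroups as secondary or exploratory. Report them as estimates with 95% confidence intervals, and do not use any of them alone to claim effectiveness. The 6- and 12-month results remain fully reported, which respects the 12-month aim. A Holm correction over the other core domains is optional.
- Reconcile the six- and seven-item lists of core outcomes.
- Disclose that for Phase 1 the confirmatory visit was fixed after data collection. For Phase 2 it can be fixed before recruitment.

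The cost is wording only: no new data and no change to the sample size. The downside is that fewer results can be presented as confirmatory, and for Phase 1 the late choice of visit weakens even the PA result as confirmatory evidence.

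### Subgroup tests are labelled as differences in intervention effect, but with three wait-list Sheds they are either barely estimable controlled contrasts or comparisons of uncontrolled change

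*Protocol article*

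**What the plan says.** The data-analysis section of Part 1 states: "Analysis of subgroups based on criteria such as; Shed size location and timing of the intervention, will also be performed". The rest of that sentence gives the purpose: the analysis "will also be performed to identify significant differences in intervention effect between groups". The significance level for inferential tests is 0.05. The sentence does not call the subgroup analyses exploratory or descriptive.

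The preceding text defines intervention effect through change scores from baseline to 3, 6 and 12 months, without naming the groups compared. The waiting group enters that section only at the end of the quantitative plan, where success rates are compared by chi-square.

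The numbers are in Participants and sampling. "In Phase 1, 421 Shedders participated across 22 clusters and these were divided into two cohorts". During delivery in the first cohort (12 clusters, 212 men), "a wait list control cohort served as a comparator"; it had 3 clusters and 89 men, drawn from a second cohort of 9 clusters and 209 men. On location: "Fourteen clusters were in urban areas and 8 were in rural areas across counties". The article does not say how the three wait-list Sheds fall by size or location.

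**The concern.** A difference in intervention effect between two kinds of Shed is a difference of differences. It needs SFL against no SFL within each kind, and then a comparison of the two results. With three untreated Sheds there is almost no material for the control side.

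What the data support more readily is a comparison of before-after change between kinds of Shed. That can differ for reasons unrelated to SFL: men in different settings may have different underlying trends, may be measured in different seasons, or may start further from their usual level and regress towards it. Timing shows this plainly. The two cohorts were recruited in March to May and in September to December 2019, and the second was followed at 6 and 12 months by telephone under COVID-19 restrictions.

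At stake is what may be concluded. Sheds were sought for their diversity of size and setting, and Phase 1 data are to inform Phase 2. A significant subgroup result under the present label would be read as SFL working better in some settings than in others, with little or no controlled evidence behind it.

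**Working it through.** **The plan's own figures.** 106 × 2.4 = 254.4, rounded up to 255. 255 × 1.2 = 306, and 306/20 = 15.3, about 15 clusters. Both reproduce. They concern the main effect only; the article gives no figure for subgroups.

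**Inputs.** SFL: 12 Sheds, 212 men, mean 212/12 = 17.7 per Shed. Wait-list: 3 Sheds, 89 men, mean 89/3 = 29.7. The design effect of 2.4 at about 20 men per cluster implies ICC = (2.4 − 1)/(20 − 1) = 0.074. Applying this ICC to change scores is an assumption, so a range of 0.01 to 0.10 is also shown. Cluster sizes are taken as equal within arm, tests as two-sided (the article does not state sidedness), and results are in SD units.

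**Reading A: SFL versus wait-list within subgroups.** Three control Sheds divide in two only as 3+0 or 2+1.

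- *3+0:* one subgroup has no control Shed, so neither its controlled effect nor the difference in effects can be estimated.
- *2+1:* estimable if between-Shed variance is pooled across cells.

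For 2+1, the variance of a Shed mean is ICC + (1 − ICC)/m:

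- SFL: 0.0737 + 0.9263/17.67 = 0.126
- Wait-list: 0.0737 + 0.9263/29.67 = 0.105

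Main effect, all 15 Sheds: SE = √(0.126/12 + 0.105/3) = 0.213.

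Difference in effects, SFL 6+6 and wait-list 2+1: SE = √[0.126 × (1/6 + 1/6) + 0.105 × (1/2 + 1)] = √(0.042 + 0.157) = 0.447, about 2.1 times the main-effect SE. The single control Shed alone supplies 0.105 of the total variance of 0.199, just over half.

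With 15 − 4 = 11 df, the multiplier for 80% power is 2.201 + 0.876 = 3.077, so the detectable difference is 3.077 × 0.447 = 1.37 SD.

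| ICC | SE of difference in effects | Detectable, 80% power | Power for 0.55 SD |
|---|---|---|---|
| 0.01 | 0.295 | 0.91 SD | 40% |
| 0.03 | 0.350 | 1.08 SD | 30% |
| 0.074 | 0.447 | 1.37 SD | 20% |
| 0.10 | 0.496 | 1.53 SD | 17% |

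An 8+4 split of SFL Sheds changes 1.37 only to 1.39. The 0.55 SD is an assumed benchmark: it is the effect for which 53 per arm (106 in total) gives 80% power two-sided. The article does not state the effect size behind the 106.

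**Reading B: change compared between kinds of Shed, all of Phase 1.** Mean size 421/22 = 19.1. Variance of a Shed mean = 0.0737 + 0.9263/19.14 = 0.122. For 14 urban versus 8 rural Sheds, SE = √[0.122 × (1/14 + 1/8)] = 0.155. With 20 df the multiplier is 2.086 + 0.860 = 2.946, so the detectable difference is 0.46 SD (0.32 at ICC 0.01, 0.50 at ICC 0.10), in SDs of change. This uses the stated 22 clusters, which the location split also sums to; the two cohorts as given sum to 12 + 9 = 21.

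**The case against.** The best defence is that Reading B is what the authors intend. The subgroup sentence follows directly on a definition of effect through change scores, no subgroup-by-arm contrast is specified, and timing of the intervention makes little sense as a criterion for SFL versus untreated within each level. On that reading the 1.4 SD figure describes an analysis nobody planned, and the comparison has reasonable precision. This stands as to precision, and the 1.4 SD must be kept conditional on Reading A. It does not save the label, because a difference in uncontrolled change is not a difference in intervention effect.

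A reader might go further and infer that the design cannot show effect modification at all. The documents do not support that. It is literally true only of a 3+0 split, and the split is not reported. With 2+1 the contrast can be estimated, though poorly. Shed size could also enter as a continuous variable rather than a two-way split.

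A reader might also infer that subgroup p-values will decide where SFL is rolled out. The article does not say so: implementation and scale-up are guided by implementation frameworks and stakeholder work, and Phase 1 data inform Phase 2 only in general terms.

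Finally, model and reporting details for subgroups are commonly left to an analysis plan. That is fair for the random effect and the intervals. The stated aim, however, is in the article, and no later model can add control Sheds.

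**Conclusion.** The concern holds as a mismatch between the stated aim and what the design supports under either reading. Under Reading A the controlled difference is not estimable (3+0), or rests in one subgroup on a single Shed (2+1), with about 1.4 SD detectable (about 0.9 to 1.5 SD over the ICC range). Under Reading B about 0.46 SD is detectable for location, but the quantity is mislabelled.

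The counting of splits is exact. The SD figures rest on an ICC implied by a design effect taken from another study, equal cluster sizes within arm, pooled between-Shed variance and, for Reading A, a two-way split with 6+6 SFL Sheds. The general limitation on non-randomisation in the article does not address this point.

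**What to change.** Replace the subgroup sentence with:

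> Shed size, location and timing of the intervention will be examined as exploratory differences in change from baseline among all Phase 1 Sheds that received SFL (both cohorts), with Shed as a random effect and the difference and 95% CI reported. These will not be described as differences in intervention effect, and no subgroup p-value will be used to claim that SFL works in one setting and not another.

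This keeps all three planned criteria and states which Sheds contribute. The cost is a change of wording and a small change to the model. The downside is that subgroup significance claims are given up.
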